## Abstract

**Background:**

Of all athletic knee injuries an anterior cruciate ligament (ACL) rupture results in the longest time loss from sport. Regardless of the therapy chosen, conservative or reconstructive, athletes are often forced to reduce their level of physical activity and their involvement in sport. Moreover, a recent review reported prevalences of osteoarthritis ranging from 0% to 13% for patients with isolated ACL-deficient (ACL-D) knees and respectively 21% to 48% in patients with combined injuries. The need for ACL injury prevention is clear. The identification of risk factors and the development of prevention strategies may therefore have widespread health and economic implications. The focus of this investigation is to assess the role of implicit and explicit motor learning in optimising the performance of a side-step-cutting task.

**Methods/design:**

A randomized controlled laboratory study will be conducted. Healthy basketball players, females and males, 18 years and older, with no previous lower extremity injuries, playing at the highest recreational level will be included. Subjects will receive a dynamic feedback intervention. Kinematic and kinetic data of the hip, knee and ankle and EMG activity of the quadriceps, hamstrings and gastrocnemius will be recorded.

**Discussion:**

Female athletes have a significantly higher risk of sustaining an ACL injury than male athletes. Poor biomechanical and neuromuscular control of the lower limb is suggested to be a primary risk factor of an ACL injury mechanism in females. This randomized controlled trial has been designed to investigate whether individual feedback on task performance appears to be an effective intervention method. Results and principles found in this study will be applied to future ACL injury prevention programs, which should maybe more focus on individual injury predisposition.

**Trial registration:**

Trial registration number NTR2250.

## Background

Of all athletic knee injuries an anterior cruciate ligament (ACL) rupture results in the longest time loss from sport [1]. Regardless of the therapy chosen, conservative or reconstructive, athletes are often forced to reduce their level of physical activity and their involvement in sport [2]. Moreover, a recent review reported prevalences of osteoarthritis ranging from 0% to 13% for patients with isolated ACL injury and 21% to 48% in patients with combined injuries [3], indicating additional long-term medical expenses [4]. The identification of risk factors and the development of prevention strategies may therefore have widespread health and economic implications.

The majority of research into noncontact ACL injury risk factors and the accompanying gender disparity has focused on the neuromuscular and biomechanical risk factors because of their potential for modification. Neuromuscular training strategies focussing on warm-up, technique, balance, strengthening and agility exercises have continued to evolve and represent an ever-increasing and equally important research focus [5-11]. Recent epidemiological data, however, suggest that in spite of these ongoing initiatives and reported early successes [5,8,12,13], ACL injury rates and the associated gender disparity have not diminished [14-16]. The disparity between positive laboratory results and actual effects on injury outcomes in high-risk female populations suggests a missing link between current research and clinical applications for neuromuscular training interventions [17]. One problem could be the difficulties with the measurements of injury rates and the difficulties with the implementation of thorough large scale injury prevention programs. Another issue could be the fact that the transition from conscious awareness during training sessions to unexpected and automatic movements during a training or game involves complicated motor control adaptations. Post-intervention lower extremity positions in the laboratory do not necessary reflect those on the field. The transition from conscious awareness during training sessions on technique in the laboratory to unexpected and automatic movements during a training or game involves complicated motor control adaptation. The purpose of this research project is to highlight the issue of motor learning in optimising sports performance in a manner consistent with ACL injury prevention.

Instructions can be an effective means of conveying goal-related information and educators commonly use them to teach and refine motor performance at all levels of skill [18]. During our intervention we will use the concept of implicit and explicit learning. Implicit motor learning refers to the acquisition of a motor skill without the concurrent acquisition of explicit knowledge about the performance of a skill that is normally processed in an automatic way, while explicit motor learning does refer to acquiring motor skills with an internal focus and specific knowledge about the performance of a skill [19]. The performance and learning of motor skills has been shown to be enhanced if the performer adopts an external focus of attention (focus on the movement effect) compared to an internal focus (focus on the movements themselves) [20].

There are ACL injury prevention programs addressing explicit rules regarding desired landing positions by emphasizing proper alignment of the hip, knee, and ankle [8-12,21-28]. However, the use of explicit strategies may be unsuitable for the control of complex motor skills [19]. It has been shown, that instructions that direct performers' attention to his or her own movements can actually have a detrimental effect on performance and learning and disrupt the execution of automatic skills, particularly in comparison with an externally directed attentional focus [20,29-32]. The exact reasons for the beneficial effects of an external focus of attention are still relatively unclear. However, trying to consciously control one's movements might interfere with the normal, automatic motor control processes, leading to a breakdown in the natural coordination of the movement [32,33]. Motor skills that are acquired explicitly tend to be less resilient under psychological [33-37] and physiological pressure [38,39], tend to interfere with the normal automatic processing of the motor schema [33,40], tend to be less durable [41] and less robust [42] when a fast response is required and explicit learning may be affected to a greater extent by an individual's intelligence than implicit learning [43-45]. Taking these benefits into account, implicit learning should be made more appealing in modern sporting arenas, since motor skills are often performed in anxiety-provoking competitions, under fatigued conditions. Having to consciously control a movement is considered to be a great disadvantage for athletes where attention to the game, players and ball and fast acting is required and thus very little or no attention could be given to a most optimal lower extremity position. A high-cognitive task will be vulnerable during a game.

In the ACL injury enigma in particular, psychological and physiological pressure is an important factor. Myklebust et al. reported that athletes are at a higher risk of suffering an ACL injury during a game than during practice [9]. Fatigue has also been proposed to be a contributor to non-contact ACL injuries [46-48]. For obvious reasons, a game constitutes more psychological and physiological stress compared to a practice session. Especially in later stages of competition, fatigue may have a cumulative, unfavorable effect on neuromuscular control and may potentially result in hazardous movement strategies [49]. The decreased capacity for controlling body movements after fatigue will potentially be more prominent when appropriate landing techniques have been taught in an explicit manner. Also, the possibility that implicit learning may immunize the athlete against the often debilitating influence of psychological stress on motor output should not be ignored.

Considering the benefits of implicit learning mentioned above, we feel that in the prevention of ACL injuries, we need to discover the possibilities of implicit learning. We use visual feedback (ie. observational learning) during our trial, where imitation of what is shown plays an important role. Imitation is the copying of body movements that is observed [50]. The human mirror system forms the foundation of observational learning [51]. Mirror neurons mediate understanding of action because neurons that represent an action are activated in the observer's premotor cortex. This automatically induced, motor representation of the observed action corresponds to that which is spontaneously generated during active action and whose outcome is known to the acting individual. Mirror neurons are visuomotor neurons that fire both when an action is performed and when a similar or identical action is passively observed [52]. A template of the movement becomes active through the mirror neurons by which the movement itself becomes clear in terms of motor actions, without high cognitive reflections [53]. This automatically induced, motor representation of the observed action corresponds to that which is spontaneously generated during active action and whose outcome is known to the acting individual. An important functional aspect of mirror neurons is therefore the relation between their ability to link visual and motor properties.

When observers see a motor event that shares features with a similar motor event present in their motor repertoire, they are primed to repeat it. The greater the similarity between the observed event and the motor event, the stronger the priming is [54]. The activation of motor representations through mere observation could have important applications in enhancing skill learning and in motor rehabilitation [55]. We therefore want to apply an intervention in which the subjects see their own performance, implicitly or explicitly. Priming will be strong, as seeing one's own performance will result in great similarity between the observed event and the executed event.

The goal of this research project is to investigate how we can train athletes individually to use certain motor patterns, that eventually become automatic. Motor learning that is offered in an implicit manner, will potentially be more robust once on the field. Our research project might give more insight in the ongoing problem of ACL injuries and might give the opportunity to more effectively implement prevention programs targeted towards the individual needs. If individual visual implicit feedback on task performance appears to be an effective intervention method, this could be applied to larger populations participating in team sports with a high risk of sustaining an ACL injury. Results and principles found in this study will be applied to future ACL injury prevention programs.

## Methods/Design

### Study design

This will be a randomised controlled laboratory study with two between-subject factors (gender and intervention group (ie. implicit, explicit and control group)) and one within-subject factor (time, ie. pretest, one week posttest and one month posttest). After consent to participate, subjects will be randomly assigned to a group based on the order in which they sign up for the initial baseline testing session. As an equal number of males and females per group (2 × intervention group and 1 × control group) is essential, stratified sampling will be carried out. The study design, procedures and informed consent are approved by the local Medical Ethical Committee (registration number 2009-142).

We take the knee abduction moment and the loading rate of knee abduction moment over time as the main variables of interest as the main training purpose of this study is to get alignment of the leg in line with the GRF. When taking the clinical relevance of an 'at risk' and a 'not at risk' abduction moment into account, we refer to the prospective study by Hewett et al. [61]. The females in that study who ruptured their ACL (n = 9) had a greater stance phase peak external knee abduction moment, -45.3 ± 28.5 Nm, compared to that of uninjured females (n = 390), -18.4 ± 15.6 Nm (P < 0.001). We considered this mean difference in knee abduction moment to be clinically relevant, as it was predictive of ACL injury occurrence in a prospective study. We therefore used the difference to calculate the power for this study. With an effect size of 0.55 (determined based on those differences of the means divided by the pooled SD) and an alpha of 0.05, we reach a power of 0.80 when including 120 subjects, which means 40 subjects (20 females and 20 males) per group (ie. implicit learning group, explicit learning group and control group). G*Power for Mac, Version 3.1.2 has been used to calculate the needed sample size.

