### Data acquisition and statistical analysis

Hip, knee and ankle joint kinematics will be evaluated at IC, peak posterior GRF and the maximum values for each of those variables. IC will be defined as the point in time when 5% of the subject's body weight is upon the force plate. The raw coordinate data will be filtered using an optimised cut off frequency.

Raw analog data from the MVICs and synchronised raw analog data (joint kinematic, joint kinetic data and GRF data) from the jump trials will be imported into Matlab (release 12, The MathWorks, Natick, MA) for data processing and identification of the variables of interest. The mean value of each MVIC will be used for normalisation of the EMG during the jump trials. Both the MVIC and trial EMG data will be processed with a linear envelope before filtering by a Butterworth filter (fourth-order, zero-phase shift, cut off frequency of 20 Hz).

Raw analog data from the force plates will be used to calculate the GRF data for each jump trial. The raw coordinate data will be filtered using an optimised cut off frequency. The GRF will be filtered using a fourth-order Butterworth filter at a cut off frequency of 100 Hz. The GRF data will be used to calculate the maximum posterior GRF during the initial-stance phase of the jump tasks.

Only the dominant leg will be analysed. In addition to the 30 trials during the intervention and retention tests, all subjects will perform five trials to begin with. These five baseline trials (without feedback) prior to the intervention will be conducted to assure homogeneity across groups on the primary outcome measures (knee abduction moment and the loading rate of knee abduction moment over time). The results of these five trials will be compared to each other using a one-way ANOVA. Multilevel analysis will be applied to examine the within and between subject effects. The learning curve with implicit versus explicit versus no feedback of the primary outcome measures over time will be analysed using SPSS 18.0 (SPSS Inc., Chicago, IL). The secondary outcome measurements will be used as explanatory variables. In addition, post-hoc Bonferroni adjustments will be conducted for the within, between and interaction effects. An alpha level of 0.05 will be set a priori.

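### The effect size of 0.55 is not the quoted mean difference over the pooled SD (1.17 or 1.69), and the stated power of 0.80 at 120 subjects does not follow for any comparison the protocol names

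*Protocol article*

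**What the plan says.** Under Study population, the protocol article takes a published prospective study as its benchmark for a clinically relevant difference in knee abduction moment. For the injured group it reports "The females in that study who ruptured their ACL (n = 9") that they "had a greater stance phase peak external knee abduction moment, -45.3 ± 28.5 Nm". This is "compared to that of uninjured females (n = 390), -18.4 ± 15.6 Nm (P < 0.001"). The article calls this mean difference clinically relevant and says that the power calculation uses it.

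The calculation then reads "With an effect size of 0.55 (determined based on those differences of the means divided by the pooled SD"), and at alpha 0.05 "we reach a power of 0.80 when including 120 subjects, which means 40 subjects (20 females and 20 males) per group". The software is named. The test, its sidedness and the comparison powered are not.

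Under Data acquisition and statistical analysis, the plan is a multilevel analysis of the learning curve in the implicit, explicit and no-feedback arms, and "post-hoc Bonferroni adjustments will be conducted for the within, between and interaction effects".

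**The concern.** The paragraph prints every input, the formula and the result, so a reader can check it directly, and it fails at both steps: from the data to 0.55, and from 0.55 to 120 subjects at power 0.80.

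At stake is what the trial can be said to detect. The paragraph asserts two different targets at once. One is 26.9 Nm. The other is 0.55 of a pooled SD, which on the quoted SDs is 0.55 × 15.96 = 8.8 Nm or 0.55 × 22.97 = 12.6 Nm, a third to a half of the first. If the 0.80 is taken at face value for the smaller target, a non-significant difference between the implicit and explicit arms could be read as stronger evidence of no effect than the design supports.

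**Working it through.** **Inputs (all from Study population).** Injured: mean −45.3, SD 28.5, n = 9. Uninjured: mean −18.4, SD 15.6, n = 390. Stated effect size 0.55, alpha 0.05, power 0.80, N = 120 as 40/40/40.

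**Step 1: does 0.55 follow from the data?**
- Difference: 45.3 − 18.4 = 26.9 Nm.
- n-weighted pooled SD: √[(8 × 28.5² + 389 × 15.6²)/397] = √[(6498 + 94667)/397] = 15.96 Nm. d = 26.9/15.96 = **1.69**.
- Equal-weight SD: √[(28.5² + 15.6²)/2] = √[(812.25 + 243.36)/2] = 22.97 Nm. d = 26.9/22.97 = **1.17**.
- SD needed for 0.55: 26.9/0.55 = **48.9 Nm**. A pooled SD cannot exceed the larger of its two components, here 28.5 Nm, so no weighting of the two gives 0.55.

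**Step 2: does 0.80 at N = 120 follow?** Power is from the noncentral t or F distribution. For two arms the noncentrality is d√[n₁n₂/(n₁+n₂)]; for 40 versus 40 and d = 0.55 this is 0.55 × √20 = 2.46.

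| Reading | Power at N = 120 | Needed for 0.80 |
|---|---|---|
| Quoted difference, d = 1.17 or 1.69; 40 v 40, two-sided | above 0.99 | 13 or 7 per arm |
| d = 0.55; 40 v 40, two-sided, one measurement | 0.68 | 53 per arm |
| Same, Bonferroni over three arm pairs (alpha 0.0167) | 0.51 | 71 per arm |
| d = 0.55; 40 v 40, one-sided | 0.79 | 42 per arm |
| Same, one-sided, Bonferroni over three pairs | 0.62 | – |
| f = 0.55; three-group ANOVA | above 0.999 | 36 in total |
| f = 0.275 (half of 0.55); three-group ANOVA | 0.76 | 131 in total |

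**Step 3: baseline adjustment.** The trial has a pretest. With correlation r between baseline and retention test, the effective effect size is 0.55/√(1 − r²). The article gives no r, so a range is shown (assumption), for 40 versus 40, two-sided:

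| r | Effective d | Unadjusted | Bonferroni, three pairs |
|---|---|---|---|
| 0.3 | 0.58 | 0.72 | 0.55 |
| 0.5 | 0.64 | 0.80 | 0.65 |
| 0.7 | 0.77 | 0.93 | 0.84 |

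**Step 4: which settings do return about 120?** Two were found.
- A two-sided t test of both feedback arms combined against control, 80 versus 40, at d = 0.55: power 0.804 at N = 120 and 0.794 at N = 117.
- A repeated-measures between-subjects F test over six gender-by-arm cells, with f = 0.275, three sessions and an assumed correlation of 0.5: N = 119.

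The protocol names neither. The first merges the two arms that the trial sets out to contrast. The second tests any difference among six cells averaged over sessions, the pretest included.

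**The case against.** Four points can be made for the plan.

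**0.55 may have a traceable origin.** Three groups with means 45.3, 18.4 and 18.4 have a root-mean-square spread of 12.68 Nm; divided by 22.97 this gives Cohen's f = 0.552. The number may therefore come from the quoted data under the wrong label. That is plausible, but it is not the formula the article states, and f = 0.55 leads to about 36 subjects rather than 120.

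**A single-measurement t test is not the planned analysis.** The design has a pretest and two retention tests, analysed by a multilevel model, which can raise power. This stands. A reader might infer that 120 subjects cannot give 0.80 for any between-arm comparison at d = 0.55. The documents do not support that: baseline adjustment at r of 0.5 or more reaches it without multiplicity correction, and an unadjusted one-sided test comes close at 0.79.

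**The error does not show underpowering for the named target.** This also stands. For the difference that the article calls clinically relevant, taking the smaller d of 1.17, a 40 versus 40 comparison has power 0.997 even at alpha 0.0167, and a 20 versus 20 comparison within one sex has 0.95 unadjusted.

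**The article is condensed, and its Bonferroni family is not defined.** The 0.51 does rest on assuming three arm pairs. But the central contradiction is not an omission: the data, the formula and the result are all printed and disagree.

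**Conclusion.** The point holds as a contradiction within the sample size paragraph. The stated derivation gives 1.17 or 1.69, two to three times the stated 0.55 (1.17/0.55 = 2.1; 1.69/0.55 = 3.1). This rests only on printed figures.

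The claim "we reach a power of 0.80 when including 120 subjects" matches neither target for a comparison of the three arms that the protocol describes. It is far too low for the 26.9 Nm difference (above 0.99). For d = 0.55 on one measurement, two-sided, it is too high (0.68, or 0.51 if three arm pairs are Bonferroni-adjusted). At d = 0.55, about 0.80 is recovered two-sided only by assuming a baseline correlation of at least 0.5 and no multiplicity correction; with the correction, power is 0.65 to 0.84 for correlations of 0.5 to 0.7.

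A reader might conclude that the trial is underpowered. That goes too far: it depends on keeping 0.55 as a d after showing that the quoted data do not produce it. What is shown is that the paragraph does not tell the reader which effect the trial is powered to detect.

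**What to change.** Keep 120 subjects and rewrite the paragraph:

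1. Delete or correct the statement that 0.55 is the quoted difference over the pooled SD. If 0.55 is a Cohen's f or comes from elsewhere, say so and show the derivation.
2. Name the effect-size metric, the contrast, the test, the sidedness and the set of comparisons covered by the Bonferroni adjustment.
3. Restate power for that contrast. For example, 40 versus 40, two-sided, gives about 80% power for d = 0.63 unadjusted or d = 0.74 with Bonferroni over three pairs. Alternatively, give the baseline-adjusted power at d = 0.55 with the assumed correlation and its source.
4. State that power for the quoted 26.9 Nm difference is above 0.99 per pair of arms.

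The cost is one paragraph and no added subjects. The downside is that the figure for small effects becomes less favourable than the 0.80 now claimed.

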### Intervention

Two types of immediate visual feedback will be given (Table 1):

**Table 1 T1:** Testing schedule

	Explicit Learning Group (n = 40)	Implicit Learning Group (n = 40)	Control Group (n = 40)
T1 Intervention	30 side-step cutting trials - Detailed verbal instructions on performance will be given	30 side-step cutting trials - Best performance will be shown	30 side-step cutting trials - No feedback on performance will be given
T2 Retention test (one week post intervention)	30 side-step cutting trials - No feedback on performance will be given	30 side-step cutting trials - No feedback on performance will be given	30 side-step cutting trials - No feedback on performance will be given
T3 Retention test (one month post intervention)	30 side-step cutting trials - No feedback on performance will be given	30 side-step cutting trials - No feedback on performance will be given	30 side-step cutting trials - No feedback on performance will be given

1) Explicit feedback: After each sidestep cutting manoeuvre, subjects will immediately receive explicit instructions to improve their performance. Potential ACL injury risk factors include: 1) Increased knee valgus angle [61], 2) Decreased knee flexion angle [62-64], 3) Increased anterior tibial shear force [65,66], 4) Decreased hip flexion angle [62,64,67,68], 5) Increased hip internal rotation angle [62], 6) Increased knee internal rotation angle [69]. Items to improve these potential risk factors above will be mentioned to the subjects and subjects will be requested to minimise the load at the knee.

2) Implicit feedback: Subjects will undergo a dynamic visual feedback intervention. Each time after a subject has performed the task, a visual representation of the best performance so far of the whole body (3D posterior view) will be shown to the subject with the Basler recordings (Darwinian learning). No explicit feedback or instructions at all will be given, however subjects will know in advance that there are superior and inferior ways to perform the task. The subject will search by him-/herself for the solution that fits best in their body; they explore and then select the performance which fits best.

The best performance so far will be based on the peak valgus moment, which needs to be as low as possible. The total training session consists of 30 trials. As we need to make sure that the improvements in landing performance (if any) are permanent rather than temporary, a retention test will be conducted one week (similar to Onate et al.) [70] and one month later. During the retention tests no feedback at all will be given to either group. The control group will perform the exact same tasks as the intervention groups. The control group, however, will not receive any feedback during any trial. To make sure three homogeneous groups are participating, five trials with no feedback will be performed prior to the real intervention (ie. in addition to the 30 trials).

